**Secondary end points**
Disease progression
Number of patients by treatment intervention with MRI/CT evidence of visible arterial enhancement, radiologic report of progression, or radiologic report of new tumor growth or symptomatic/clinical progression.
Time to disease progression
Number of days from date of treatment initiation to date of documented disease recurrence based on MRI or CT by treatment intervention, or symptomatic/clinical progression. Patients without recurrence will be censored from last date of treatment assessment.
Complication rate
Number of patients by treatment intervention who were withdrawn due to adverse events prior to introduction of other therapy.
Time to treatment-limiting adverse events
Number of days from first date of treatment to date of withdrawal due to adverse event(s) prior to introduction of other therapy. Patients without treatment-limiting adverse events will be censored at last date of treatment assessment.
Treatment failure rate
Number of patients by treatment intervention with a finding of treatment switch, HCC-related hospitalization and emergency room visit, disease recurrence, or death prior to introduction of other therapy.
Time to treatment failure
Number of days to first treatment failure overall and by individual item. Patients without treatment failure will be censored from last date of treatment assessment.

CT, computed tomography; MRI, magnetic resonance imaging.

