### Data analysis

To evaluate therapeutic approaches to HCC in China, the number and percentage of patients using each treatment (plus any new treatments that are approved and used within the study period) will be determined for each study year, in total and stratified by disease stage and site. Treatment patterns will also be assessed by disease stage for each study year. Patient characteristics will be stratified by disease stage and by site for each study year.

To assess therapeutic outcomes, age- and gender-adjusted rates will be calculated for each study end point. Cox proportional hazard models will be used for the time-to-event end points (overall survival and disease progression) to determine hazard ratios for each treatment approach, and Kaplan-Meier curves will be generated. Logistic regression models will be used for categorical end points (treatment-limiting adverse events and treatment failure). Covariates for the models will include disease stage, gender, age, duration of disease, etiology of disease, liver status, tumor size/spread, surgical intervention/number of interventions, and number of comorbidities; analyses will be conducted at the site and country level. The same analysis plan will be adopted for the evaluation of survival and other clinical end points with sorafenib versus other therapies, except that "treatment" will be included as a covariate. Further analyses will be conducted to evaluate clinical characteristics and demographics of patients treated with sorafenib versus other treatments for HCC. In addition, data collected will be used to analyze additional aspects related to HCC epidemiology and management in China (Table 2). All tests of statistical significance will be carried out at the 0.05 level.

**Table 2 T2:** Additional aspects of HCC management for potential evaluation using data from the HCC BRIDGE China national study.

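### Table 1 counts, times and censors disease progression on three different event sets, and treatment failure counts HCC-related hospitalization without excepting admissions that deliver planned treatment

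*Protocol article*

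**What the plan says.** Table 1 of the protocol article (Secondary end points) gives separate rows for the number of patients with progression and for the time to it.

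- **Count.** Patients with "MRI/CT evidence of visible arterial enhancement, radiologic report of progression, or radiologic report of new tumor growth or symptomatic/clinical progression".
- **Time.** "Number of days from date of treatment initiation to date of documented disease recurrence based on MRI or CT by treatment intervention". The sentence goes on, so that the event wording in full is "documented disease recurrence based on MRI or CT by treatment intervention, or symptomatic/clinical progression".
- **Censoring of the time.** "Patients without recurrence will be censored from last date of treatment assessment".
- **Treatment failure.** Patients "with a finding of treatment switch, HCC-related hospitalization and emergency room visit, disease recurrence, or death prior to introduction of other therapy". A further row reports time to treatment failure, overall and for each component.

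The Data analysis section assigns Cox models to overall survival and disease progression, to give a hazard ratio per treatment approach. It assigns logistic regression to treatment-limiting adverse events and treatment failure. The same plan is used for sorafenib against other therapies. The Background lists the treatments involved: resection, transplantation, ablation, hepatic artery infusion, chemoembolization, and systemic options including sorafenib.

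**The concern.** The time row is the only one that gives progression a time, so it is what a Cox model would use. It does not name two of the imaging findings that the count accepts: radiologic progression and arterial enhancement. It uses *recurrence*, a word that suits patients who were made tumor-free. Some compared treatments aim at that state and others usually leave tumor in place. If the wording is applied literally, whether an imaging event is recorded depends on the treatment received. Adjusting for prognostic covariates does not repair an outcome that is ascertained differently by treatment.

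Treatment failure raises a similar problem. Surgical and interventional treatments commonly need an admission, and oral treatment generally does not. With no exception for admissions that deliver planned treatment, giving or repeating an inpatient procedure can be recorded as its failure.

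At stake are the secondary treatment comparisons on progression and treatment failure.

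**Working it through.** The article gives no rates for these end points and no figure that depends on them, so there is nothing to reproduce. The check is a comparison of the wording, followed by illustrations on assumed inputs.

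**1. The progression wording side by side**

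| Finding | Count row | Time row | Censoring sentence |
|---|---|---|---|
| Visible arterial enhancement | event | not named | censored unless called recurrence |
| Radiologic report of progression | event | not named | censored unless called recurrence |
| New tumor growth on imaging | event | event only if called recurrence | censored unless called recurrence |
| Recurrence on MRI or CT | not named as such | event | not censored |
| Symptomatic/clinical progression, no recurrence | event | event | censored |

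Two things follow. Imaging growth of a tumor that was never cleared is counted but, read literally, not timed. A patient with clinical progression and no recurrence is an event under one sentence and censored under the next. In addition, the count row does not require enhancement to be new or increased, so residual stable tumor can be counted as progression.

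**2. Progression: illustration on assumed shares**

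Let the true progression hazard be equal in two groups. In one group every counted event qualifies for timing. In the other only a share *s* does. If the remaining events never qualify later:

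apparent hazard ratio = *s* × hazard ÷ hazard = *s*

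- *s* = 1.0 (sites take recurrence to include progression): 1.0, no distortion
- *s* = 0.8: 0.8
- *s* = 0.5: 0.5
- *s* = 0.3: 0.3

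These are limiting values. A patient whose imaging growth is not timed stays at risk until the last treatment assessment and may still become an event through clinical progression. Some events are therefore delayed rather than lost, and the distortion is then smaller.

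**3. Treatment failure: illustration on assumed rates**

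Let true failure be *p* = 50% in both groups. In one group a share *q* has a planned HCC-related admission that is recorded as failure, independently of true failure. The other group has none.

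observed failure = 1 − (1 − *p*)(1 − *q*) = 1 − 0.5(1 − *q*)

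The odds in the other group are 0.5 ÷ 0.5 = 1, so the odds ratio equals the odds of observed failure. The last column assumes 100 patients per group and a two-sided 0.05 test of two proportions.

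| *q* | Observed failure | Odds ratio (true 1.0) | Chance of a significant result |
|---|---|---|---|
| 10% | 1 − 0.5 × 0.9 = 55% | 0.55 ÷ 0.45 = 1.22 | 10.5% |
| 30% | 1 − 0.5 × 0.7 = 65% | 0.65 ÷ 0.35 = 1.86 | 57% |
| 50% | 1 − 0.5 × 0.5 = 75% | 0.75 ÷ 0.25 = 3.0 | 96% |
| 90% | 1 − 0.5 × 0.1 = 95% | 0.95 ÷ 0.05 = 19 | about 100% |

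**4. Two ambiguities in the failure row**

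The row joins hospitalization and emergency room visit with *and*, which may mean either one or both together. It also lists a treatment switch as an event and ends by restricting events to the time before another therapy starts. If that restriction governs the whole list, a switch, which starts another therapy, could not qualify. If it governs only death, there is no conflict.

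**The case against.** The strongest reply is that *recurrence* here is a loose synonym for imaging progression. The row is titled as time to progression and follows directly on the progression row. On that reading *s* = 1 and the hazard ratios are undistorted. This stands as a possible reading. But the article does not state it, the row directly above uses different terms, and the censoring sentence still conflicts with the time row on clinical progression. A result that depends on how each site reads a word is not well defined.

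For sorafenib, historic controls are matched on age, sex, Child-Pugh status and HCC stage, and the models adjust for stage, tumor size or spread and surgical intervention. This should narrow the gap between curative and non-curative treatment in that comparison. It does not change what is recorded as an event.

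Time to treatment failure is also reported by component, so the admission component can be seen separately. That helps only in part, because the logistic model uses the composite.

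Four stronger readings are tempting, and the article does not support them:

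- *Progression is timed to recurrence only.* The time row also includes symptomatic or clinical progression.
- *The hazard ratios must favor non-curative treatment, including sorafenib, whatever the true effect.* The wording can add bias; its size depends on rates and site practice that the article does not give.
- *Failure approaches 100% for inpatient procedures.* That is a limiting case in which nearly every treatment-delivery admission is recorded as failure. Nor does the article say that outpatient therapy has no HCC-related admissions.
- *A switch can never count as failure.* This depends on how the closing restriction is read.

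**Conclusion.** The point holds as a defect of definition in secondary end points. The count, time and censoring of progression use three different event sets, and two of them contradict each other on clinical progression without recurrence. Treatment failure has no exception for admissions that deliver planned treatment. Both can create a difference between treatments where none exists, but neither excludes a real difference.

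The size cannot be derived from the article. The illustrations rest on equal true risk in both groups and on assumed shares. They give apparent progression hazard ratios from 1.0 (no distortion) down to 0.3 as a limiting case, and failure odds ratios from 1.22 at 10% planned admissions to 3.0 at 50%. Overall survival, the primary end point, is unaffected. The change should be made, but the study's main result does not depend on it.

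**What to change.** In Table 1:

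- **Progression.** Use one event list for count, time and censoring: the first of radiologic progression, new tumor growth, recurrence, or symptomatic/clinical progression. Accept arterial enhancement only if it is new or increased against the imaging at treatment start.
- **Censoring.** Censor patients without progression, in place of patients without recurrence.
- **Treatment failure.** Exclude admissions that deliver planned treatment. State whether hospitalization and emergency room visit means either or both. Make clear that the restriction to events before another therapy does not apply to the switch item.

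The wording change costs little. The practical cost is coding the reason for admission and the comparison with earlier imaging. The charts are already being reviewed for hospitalizations and tumor assessments, but with about 9000 patients expected and no fixed assessment times this is some additional work, and some records may not allow the comparison.

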In recent years, the China Ministry of Health has made great strides in the management of HCC by establishing it as one of 5 tumors of high national importance and by initiating a number of primary HCC prevention activities. These include providing government-funded HCC screening for persons in high-risk areas (within the Jiangsu and Guangxi provinces) who are positive for hepatitis B surface antigen and who have cirrhosis and, more recently, enacting mandatory hepatitis B virus vaccination programs. Despite these advances, HCC remains a cancer with a high mortality rate and a clear unmet medical need in China. Based on data from the Third China National Mortality Survey conducted in 2004/2005, HCC is the second leading cause of cancer mortality in cities and the leading cause in rural areas [9]. Moreover, this survey reported an HCC mortality rate in China of 26 deaths per 100,000 persons. When considering these mortality data, it is important to acknowledge that they are pooled from individual studies supported by the China Ministry of Health, and only represent certain regions of the country. As such, the reported national mortality rate may not accurately reflect the true burden of HCC across the country. Furthermore, given the lack of active surveillance, there remain many unanswered questions surrounding the epidemiology and management of HCC in China.

The global HCC BRIDGE study is an ongoing longitudinal cohort trial of patients with HCC in 3 core geographic regions (Asia-Pacific, European, and North American) that is designed to (1) evaluate current treatment approaches to HCC and associated clinical outcomes, and (2) determine the real-world impact on clinical outcomes of new HCC treatments, such as sorafenib, versus other therapies [10]. Recently, the HCC BRIDGE study was expanded as a national study in China allowing a specific and more detailed evaluation of HCC across this important country.

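### Kaplan-Meier curves for time to progression censor deaths without recorded progression, so one minus the curve overstates the probability of progression

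*Protocol article*

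**What the plan says.** Table 1 (End points, secondary end points) measures time to disease progression in days from the start of treatment to recurrence shown on MRI or CT, or to progression judged clinically or from symptoms. Death is not part of the event. The censoring rule that follows is "Patients without recurrence will be censored from last date of treatment assessment", with nothing said about patients who have died.

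Two neighbouring definitions in the same table do deal with death. The overall survival rule restricts censoring to surviving patients, and the treatment failure composite lists death as one of its components. Time to progression does neither.

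Data analysis fixes the method: "Cox proportional hazard models will be used for the time-to-event end points (overall survival and disease progression) to determine hazard ratios for each treatment approach". For the graphical display, the same sentence adds that "Kaplan-Meier curves will be generated". No cumulative incidence or other competing-risk method is named for progression. The Background section says that "HCC remains a cancer with a high mortality rate and a clear unmet medical need in China". Under Study design, follow-up runs from diagnosis (1 January 2005 to 30 June 2011) to death or 31 December 2011, so potential follow-up is between about half a year and seven years.

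**The concern.** Kaplan-Meier treats a censored patient as someone who could still have the event later, at the same rate as those still under observation. That is reasonable for a patient whose follow-up stops at the end of the study. It is not true of a patient who has died, because that patient can no longer progress. If such patients are censored, one minus the curve estimates what would be seen if nobody died first, not the proportion of patients who actually progress.

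At stake is how the progression curves are read. In a disease that the article itself describes as having high mortality, a progression probability taken from the curve would be too high. If death without recorded progression is more common under one treatment than another, the curves are inflated by different amounts, and the visual comparison mixes a difference in progression with a difference in mortality.

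**Working it through.** The article states no progression rate, death rate or event count for this end point, so there is no figure of its own to reproduce. The direction of the error follows from the written rules. The size can only be illustrated.

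**Inputs from the article:** the event is progression only; everyone without it is censored at the last treatment assessment; the curve is Kaplan-Meier.

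**Assumed inputs:** constant yearly hazards, *hp* = 0.8 for progression, and *hd* = 0.08, 0.2, 0.4 or 0.6 for death without progression (10% to 75% of *hp*).

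**Formulas:**
- One minus Kaplan-Meier with deaths censored: 1 − exp(−hp·t)
- Actual cumulative incidence of progression: hp/(hp+hd) × [1 − exp(−(hp+hd)·t)]

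**At 2 years,** 1 − KM = 1 − exp(−1.6) = 79.8% whatever the death hazard. The cumulative incidence is:
- hd = 0.08: (0.8/0.88) × (1 − exp(−1.76)) = 75.3%
- hd = 0.2: (0.8/1.0) × (1 − exp(−2.0)) = 69.2%
- hd = 0.4: (0.8/1.2) × (1 − exp(−2.4)) = 60.6%
- hd = 0.6: (0.8/1.4) × (1 − exp(−2.8)) = 53.7%

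**At 1 year,** 1 − KM = 1 − exp(−0.8) = 55.1%, and the second formula with t = 1 gives the last two columns below.

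| hd per year | 2-year incidence | Overstatement (points) | 1-year incidence | Overstatement (points) |
|---|---|---|---|---|
| 0.08 | 75.3% | 4.5 | 53.2% | 1.9 |
| 0.2 | 69.2% | 10.6 | 50.6% | 4.5 |
| 0.4 | 60.6% | 19.2 | 46.6% | 8.5 |
| 0.6 | 53.7% | 26.1 | 43.1% | 12.0 |

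The constant 79.8% also shows the effect on comparisons. Two treatment groups could have the same Kaplan-Meier curve while their actual 2-year probabilities of progression differ by 75.3 − 53.7 = 21.6 points.

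**Simulation check** (200,000 patients, other assumed rates: median time to progression 12 months, death hazard half the progression hazard). The closed form gives 50.0% against 43.1% at 12 months and 75.0% against 58.3% at 24 months. The simulation gives 50.2% against 43.2% and 75.1% against 58.4%. Moving each censoring time back to an assumed 3-monthly last assessment, closer to the written rule, raises the Kaplan-Meier figures a little further, to 52.0% and 77.1%.

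**Wider range.** With assumed medians of 6 to 24 months, death hazards of 0.1 to 1.0 times the progression hazard, and readings at 12 and 24 months, the overstatement runs from 0.5 to 43.9 points.

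**The case against.** The other side has several good points.

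- **Clinical progression counts as an event.** A reader might infer that every patient who dies before imaging is censored. The definition does not support this: a patient who deteriorates clinically from the tumour and dies without a scan can already be an event. Only deaths with neither imaging nor clinical progression on record are at issue. That favours the low end of the range but does not remove the problem.
- **The stated treatment comparison is the Cox model.** With deaths censored, its hazard ratio is a valid cause-specific hazard ratio. This stands in full; the fault lies in the curve and in probabilities read from it.
- **Tabulated results.** A reader might infer that tabulated treatment comparisons are biased too. Table 1 counts patients with progression separately, and Data analysis adds age- and gender-adjusted rates. Neither is said to come from Kaplan-Meier, so the inference has no support in the text.
- **Adverse events.** Table 1 has a parallel rule for time to treatment-limiting adverse events: "Patients without treatment-limiting adverse events will be censored at last date of treatment assessment". A reader might extend the criticism to it. However, Data analysis assigns that end point to logistic regression and states no Kaplan-Meier curve for it.
- **Sorafenib.** A reader might expect sorafenib-treated or advanced-stage patients to be distorted most. The distortion depends on death without progression relative to progression, not on mortality alone, and the article gives neither hazard by treatment or stage.
- **Death is counted elsewhere,** in overall survival and in treatment failure. True, but treatment failure also includes treatment switch and HCC-related hospital use, so it does not replace a correct progression curve.
- **Competing-risk detail often sits in the analysis plan.** That would answer a complaint of omission. Here the article itself fixes both the censoring rule and the type of curve.

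**Conclusion.** The point holds for the progression curve. Followed as written, the plan censors patients who die without recorded progression, and one minus Kaplan-Meier overstates the probability of progression whenever there are such deaths. Comparisons of the curves are distorted if those deaths differ by treatment; the article neither shows nor excludes this.

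The size is not derivable from the article. Under constant hazards of 0.8 per year for progression and 0.08 to 0.6 per year for death without progression, it is about 4.5 to 26 points at 2 years. Other plausible rates would give less or more.

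The Cox analysis of progression and the overall survival end point are not called into question. The point concerns the presentation of a secondary end point. It should be corrected because the curve is misleading and the correction is cheap.

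**What to change.** In Data analysis, limit the Kaplan-Meier statement to overall survival and show disease progression by cumulative incidence (Aalen-Johansen) curves with death as a competing event. Keep the Cox model for progression and label its result a cause-specific hazard ratio. Optionally add progression-free survival, with progression or death as the event, as a supporting analysis. In Table 1, state that death without recorded progression is a competing event and not ordinary censoring.

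For treatment-limiting adverse events no Kaplan-Meier curve needs replacing. Only if the Table 1 time variable is plotted should cumulative incidence be used there as well.

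The cost is a change of wording and slightly more analysis work with routine software. No new data are needed, since deaths and their source are already collected, although the Loss to follow-up section expects that deaths cannot be verified for 5% of patients. Reported progression probabilities will be lower than the Kaplan-Meier figures, which may hinder comparison with reports that used Kaplan-Meier.

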## Background

Hepatocellular carcinoma (HCC), one of the world's most prevalent and deadly malignancies [1,2], is particularly common in Asia-Pacific countries, with more than half of all cases occurring in China alone [2,3]. In most patients, HCC develops in association with liver cirrhosis and/or viral hepatitis infection. Indeed, the main risk factors for the development of HCC among the Chinese population are the presence of liver cirrhosis and chronic infection with hepatitis B virus [4]. Other risk factors include chronic hepatitis C virus infection, a family history of liver cancer, depression, ingestion of aflatoxin B1 via contaminated foodstuffs, and excessive alcohol consumption [4,5].

Current therapeutic options for HCC in China are varied, with treatment allocation generally dependent on the patient's liver function and tumor burden. Commonly used therapies include surgical techniques, such as liver resection and liver transplantation; interventional therapies, such as hepatic artery infusion and transcatheter arterial chemoembolization; and ablation techniques, such as anhydrous alcohol injection and radiofrequency or microwave ablation [6]. Systemic therapy options, including radiotherapy, immunotherapy, standard chemotherapy, and traditional Chinese herbal medicines, are also recommended [6]. In addition, the multikinase inhibitor sorafenib, which has demonstrated a reduction in death risk among advanced, inoperable HCC patients with mostly Child-Pugh A cirrhosis [7,8], is approved in China for treatment of advanced unresectable HCC.

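### The complication rate counts only withdrawals for adverse events, so single-session surgery scores close to zero by construction and comparisons tend to disfavour continuing drugs

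*Protocol article*

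**What the plan says.** All of this is in the protocol article.

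- **End points, Table 1, complication rate:** "Number of patients by treatment intervention who were withdrawn due to adverse events prior to introduction of other therapy".
- **Table 1, companion time-to-event row:** "Number of days from first date of treatment to date of withdrawal due to adverse event(s) prior to introduction of other therapy". On censoring: "Patients without treatment-limiting adverse events will be censored at last date of treatment assessment". The event is the same withdrawal. Nothing says how it applies to a treatment that is complete after one session.
- **Background, treatments in use:** these include "surgical techniques, such as liver resection and liver transplantation", and also "interventional therapies, such as hepatic artery infusion and transcatheter arterial chemoembolization; and ablation techniques". Sorafenib and other systemic options stand beside them.
- **Data analysis, model:** "Logistic regression models will be used for categorical end points (treatment-limiting adverse events and treatment failure", with disease stage, tumor size/spread and a covariate for surgery and number of interventions among the adjustments.
- **Data analysis, sorafenib contrast:** "The same analysis plan will be adopted for the evaluation of survival and other clinical end points with sorafenib versus other therapies", with treatment added as a covariate.
- **Comparator groups:** historic controls are matched to sorafenib patients on age, sex, Child-Pugh status and HCC stage. Concurrent controls are patients on non-sorafenib therapies, procedures not excluded, and are used to compare patient characteristics.

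The limitations listed in the Discussion do not mention how this end point behaves across types of treatment.

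**The concern.** Withdrawal needs something to withdraw from. A drug taken until toxicity or progression can be stopped, and so can a planned series of sessions. A resection or transplantation is finished when the patient leaves the operating theatre. A severe complication afterwards is not a withdrawal and is not counted.

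The two rows built on this event are the only safety end points in Table 1. Tabulated by treatment and modelled with treatment as a covariate, they combine how toxic a treatment is with whether it can be stopped. The second part pulls single-session surgery towards zero and makes continuing drugs look worse by comparison. The row's label adds to the problem, because a reader will take a low complication rate after surgery at face value. Comparing sorafenib with other therapies is a stated aim of the global study, so this falls on a contrast that matters.

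There is also a modelling consequence. If treatment enters the logistic model as separate categories and one category has no events, its odds ratio has no finite maximum-likelihood estimate.

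**Working it through.** The article gives no adverse event rate, withdrawal rate or treatment mix, so there is no stated figure to reproduce. The definition can be checked by reasoning; the size can only be illustrated.

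**1. Which treatments can have the event**

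| Treatment | Can the patient be withdrawn? | Effect on the count |
|---|---|---|
| Resection, transplantation | No, once completed | Zero or near zero |
| Ablation, chemoembolization, arterial infusion | Yes, if a repeated course is stopped | Undercount possible, smaller |
| Sorafenib, other continuing drugs | Yes | Counted |

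Between two continuing drugs the problem does not arise.

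**2. Crude illustration (all inputs assumed)**

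- p = 0.10: the same risk in every group of an adverse event serious enough to stop a continuing treatment.
- f: share of comparator patients whose treatment was a single session, with no withdrawal possible.
- Counted comparator rate: q = (1 − f) × p.
- Crude odds ratio for sorafenib: OR = [p/(1 − p)] / [q/(1 − q)], where p/(1 − p) = 0.10/0.90 = 0.1111.

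| f | q | q/(1 − q) | OR |
|---|---|---|---|
| 0 | 0.10 | 0.1111 | 1.00 |
| 0.30 | 0.07 | 0.0753 | 1.48 |
| 0.50 | 0.05 | 0.0526 | 2.11 |
| 0.70 | 0.03 | 0.0309 | 3.59 |

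The true odds ratio is 1.0 in every row.

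**3. What the surgical covariate does (p = 0.10, f = 0.50)**

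- *It identifies every single-session patient, and no sorafenib patient had surgery.* The zero-event stratum holds comparators only and says nothing about sorafenib. The remaining comparators have a rate of 0.10, so OR = 1.00.
- *It identifies half of them.* Per 100 comparators, 25 are removed; 50 continuing and 25 unidentified single-session patients remain. Their rate is 0.10 × 50/75 = 0.0667, with odds 0.0714. OR = 0.1111/0.0714 = 1.56.
- *It identifies all of them, but 20% of sorafenib patients also had surgery, with the same 10% event rate.* With equal group sizes, the cells per 100 are: sorafenib 80 without and 20 with surgery, each at 10%; comparators 50 without surgery at 10% and 50 with surgery at 0%. A main-effects logistic fit gives OR = 1.60.

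Adjustment can therefore remove the artefact entirely or leave a good part of it, depending on how surgery is coded and who had it.

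**4. Separation**

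In a treatment-specific model, a category with q = 0 has no finite odds ratio. In the pooled sorafenib contrast, q is 0.03 to 0.07 in the rows above with f > 0, so the treatment odds ratio stays finite.

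**The case against.** The case on the other side is substantial.

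- **The odds ratios are crude; the planned models are adjusted.** This stands. The surgical covariate can bring 2.11 down to 1.00 in the favourable case. The other two cases above show that it need not.
- **The comparator shares are guesses and may be too high.** This largely stands. Historic controls are matched on stage, and the Background says sorafenib is approved in China for advanced unresectable disease, so matched controls should include few resections. The Data analysis section's broader wording on sorafenib versus other therapies is not confined to matched controls, so some exposure remains.
- **The end point is elsewhere named treatment-limiting adverse events, which is accurate.** This stands for the abstract, the End points text and the Data analysis section. The misleading label is in one row of Table 1.
- **Severe procedural complications can appear under treatment failure**, through HCC-related hospitalization and emergency visits or death. Some can, but they are still missing from the safety row.
- **The article condenses a fuller protocol that may say how withdrawal applies to procedures.** Possible. However, the definition and the comparison are both stated here and do not fit together as stated.
- **Withdrawal has no stated object.** The companion end point's name points to withdrawal from treatment. Withdrawal from the study would not measure complications either.

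A reader might go further and infer that the study will report surgery and ablation as free of complications, or that the sorafenib model will fail to converge. The article supports neither. Ablation may be repeated and a course stopped. Separation arises only if treatment enters as categories and one has no events.

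**Conclusion.** The point holds as a defect in how a secondary safety end point is defined and compared. Counting only withdrawals gives resection and transplantation zero or near-zero events by construction, and the planned logistic comparison then tends to disfavour continuing drugs. For procedures that may be repeated, any bias is in the same direction but smaller.

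Its size is unknown. The crude odds ratios of 1.5, 2.1 and 3.6 rest on an assumed equal 10% risk and assumed single-session shares of 30%, 50% and 70%. They are unadjusted illustrations, not predictions of what the study will report. A reader might take them as the expected bias in the sorafenib result. The documents do not support that, because stage matching and the listed covariates would shrink it, possibly to nothing. They would not do so reliably.

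The change is worth making, but the primary end point, overall survival, is not affected.

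**What to change.** 1. Rename the Table 1 row *withdrawal due to adverse events*.
2. Restrict the between-treatment comparison and logistic model for this end point, and the companion time-to-event end point, to treatments given continuously or in repeated courses, where withdrawal is possible.
3. Report adverse events after single-session procedures in a separate descriptive table, if the data capture holds them. The abstract lists adverse events among the data collected, but the itemised list under Data collection does not, so the sponsor should confirm this first.

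**Cost:** wording, a restricted analysis set for one end point and its time-to-event companion, and one extra table if the data exist. If they do not, that table cannot be produced without further chart review. The scientific cost is that no single safety comparison would span all treatments.
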